### Recruitment and eligibility of primary care physicians

GPs are eligible for participation if they provide care in the routine primary setting (single handed practices and group practices) to unselected patients.

About 300 GPs in the area of Zurich and Winterthur are invited to an information meeting by a formal letter of the Institute of General Practice and Health Services Research of the University of Zurich and the Department of Health of the Canton of Zurich. In this information meeting an overview of the study will be given. The main focus of the first information meeting for all GPs is to present the project and to motivate GPs to take part in the study. Additionally, the project will be presented in several quality circle meetings in doctors’ networks (regions Zurich, Winterthur).

GPs who agree to participate will be randomized, stratified by practice organization (single handed versus group practices). All participating GPs/practice assistants will receive instruction by a pneumologist and a spirometry technician in performing a spirometry. Practices in the intervention group get detailed information on evidence-based COPD management and ‘QualiCCare’ training sessions and instruments, designed to increase knowledge, internal motivation and decision-making and to support incorporation of evidence into their daily work (details described in the intervention section).

The GPs of the control group apply ‘care as usual’ without receiving the ‘QualiCCare’ training and implementation tools.

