### Outcomes

#### Primary outcome

Difference in ‘quality of care process’ (total increase in performed measures/fulfilled indicators) after one year between COPD patients in the intervention and control group as reported by the patient (described below).

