### Data collection procedures

#### Patient questionnaire

The patients will receive detailed written information on the aim of the study. After giving their written informed consent they will receive a questionnaire (T0) assessing gender, age, employment status, and family background, the CAT, information on respiratory symptoms (cough, sputum, dyspnea), and severity of dyspnea (Medical research council MRC dyspnea scale), smoking status, motivation to quit, exacerbations and health care utilization (including unscheduled visits, emergency department attendances and hospital admissions due to pulmonary problems). Patients are asked at T0 whether, in the previous year before study inclusion, they had received: advice to quit smoking, assessment and advice for physical activity or advice/referral to pulmonary rehabilitation, recommendation/application of influenza vaccination, patient education with defining COPD and information about the main causes, signs and symptoms, information on medication and using inhalation devices with face-to-face instruction and demonstration of inhalation technique, information on how to identify and manage an aggravation of symptoms (exacerbation) and an action plan for exacerbation management including medication adjustment for exacerbation treatment. In addition patients are asked whether they have received COPD support by community resources (lung associations, support groups) and other specialized health professionals. Patients are asked the same questions one year after study inclusion T1. They receive the questionnaires and stamped envelopes with the postal address of the university and are asked to return the questionnaire in the envelope to the university at T0, and T1 after 12 months.

Patients will also be informed that neither the GP nor the practice team has any possibility of obtaining knowledge of their answers.

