#### Data analysis

A *t*-test will be used for independent group comparisons in the primary outcome between control and intervention group. Each quality indicator itself can also be regarded as a binary outcome (performing a specific procedure (yes/no)). To analyze these binary outcomes separately logistic regression will be used to model the relationships between the outcome and treatment group, age and gender. Other potentially important covariates will be identified through exploratory analyses. The longitudinal aspect of the data can be incorporated into the model in various ways; we will utilize the generalized estimating equations (GEE) approach [31].

For continuous outcomes such as quality of life (QoL) instruments, repeated measures analysis of variance is appropriate [32].

Fixed effect parameters will include treatment group, age, gender, and other potentially important covariates. The primary data analysis will follow the intent-to-treat (ITT) approach where appropriate. This means that all available data from all individuals will be analyzed according to treatment group assignment, regardless of whether or not each individual actually received the assigned treatment.

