### Timeframe of the study

The recruitment of the 30 GPs is planned over two months between July and August 2013 (−T2).

Patient eligibility screening and patient inclusion is projected within a period of three months (−T1). The intervention courses will start subsequently.

Assessments will be made as described above, T0 baseline assessments start from the inclusion; at baseline, data regarding COPD management in the year before inclusion will also be assessed retrospectively from the patient charts and transferred anonymously to the study center.

Final measurements (T1) will be performed one year after the ‘QualiCCare’ intervention.

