## Discussion (expected results)

Improving care for people with chronic diseases is one of the big challenges in health care worldwide [17]. In this era plagued by ever-tightening health care resources, it is of utmost importance to identify and implement interventions that are of added value to quality and efficiency of care [14,33]. Efficient professional interventions and care pathways, which detail essential steps in the care of patients, have the potential for improving patient care by reaching quality standards and decreasing unwarranted practice variation. However, evaluation of their impact is important. According to Lemmens *et al*. [34] improvement of expertise, information and resources will affect behavioral intention, which leads to professional behavioral change and this should lead to improved health effects. We expect that the ‘QualiCCare’ intervention can be implemented into primary care practices and will constitute a path forward for better quality in COPD care. After adjusting for age, gender, number of chronic conditions, participating sites are expected to show significant improvement for several quality indicators, including smoking cessation advice, influenza vaccination, appropriate medical therapeutics, rehabilitation and self-management education efforts and better proactive, collaborative care compared to the ‘usual care’ group.

Professional support and improvement in these processes is the first step towards improved clinical outcome measures as quality of life and therefore, we also expect a significant difference for our secondary outcome QOL assessed by the patient.

In addition, we try to identify professional behavior change mechanisms and gain insight into some implementation processes that could help to open the ‘black box’ that frequently lies between input and outcome of interventions.

The vision that emerges from our study is of organizations that aim to implement best practice and to improve the value of care in COPD, one of the world’s major chronic illnesses. This study is, therefore, of great interest not only from the patient perspective but also from a health care system perspective.

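### The primary t-test leaves out the T0 score and the randomisation stratum; the cost is precision and protection against baseline imbalance, not planned power

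*Protocol article*

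**What the plan says.** **Primary test.** The Data analysis section of the protocol article names a t-test that "will be used for independent group comparisons in the primary outcome between control and intervention group". It lists no covariate for it.

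**Test variable.** The Primary outcome section speaks of a "total increase in performed measures/fulfilled indicators" after one year, which can be read as a change from T0. The sample size section plans on the level of the score: mean 4, SD 2.3, difference 1.5.

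**Baseline measure.** Under Patient questionnaire, T0 asks about care received in the year before inclusion, and "Patients are asked the same questions one year after study inclusion T1". Under Timeframe of the study, patient inclusion comes first and "The intervention courses will start subsequently". The T0 answers therefore precede the intervention.

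**Stratum.** GPs are randomised "stratified by practice organization (single handed versus group practices"). The statistical sections do not mention this factor again.

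**Other models.** Logistic regression for the separate binary indicators uses treatment group, age and gender. The next sentence reads "Other potentially important covariates will be identified through exploratory analyses". After the repeated-measures model for continuous outcomes, the fixed effects are again left open beyond treatment, age and gender. The Discussion expects indicator improvements "After adjusting for age, gender, number of chronic conditions".

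**The concern.** The T0 score measures the outcome itself before the intervention, and is likely to be the best single predictor of the T1 score. A t-test on T1 alone throws that information away. A t-test on the increase uses it by subtraction, which corrects fully for a baseline difference even though such differences only partly persist to T1. Adjustment for T0 as a covariate avoids both faults.

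This matters more here than in a trial that randomises 240 individuals. Only 30 GPs are randomised, and the outcome describes what GPs do, so a chance difference between arms in prior quality of care is plausible. If practice organisation is related to the score, a test that ignores the stratum also leaves in its standard error variation that the stratified allocation has balanced out.

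A smaller, separate matter is that the secondary models have an open covariate list with no selection rule, so their adjusted results can depend on choices made after the data are seen.

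**Working it through.** **Inputs from the sample size section and abstract:** SD 2.3, difference 1.5, ICC 0.04, 15 GPs per arm with 8 patients each (120 per arm, 240 in all), two-sided alpha 5% (sidedness is not stated; two-sided is assumed).

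**Assumed, not in the document:** T0–T1 correlation r of 0.3 to 0.7; equal SD and ICC at T0 and T1; the same r within and between GPs; an analysis that accounts for clustering.

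**1. The plan's own figure.** Unclustered n per arm = 2 × (2.3 × (1.960 + 1.282) / 1.5)² = 49.4. The design effect is 1 + 7 × 0.04 = 1.28, and 49.4 × 1.28 = 63.2, so 64 per arm or 128 in all. The planned 240 is not reproduced; the stated inputs need fewer. At 240 the effective number per arm is 120 / 1.28 = 93.75 and SE = 2.3 × √(2/93.75) = 0.336. Power is 99.4%, or 99.0% with a t distribution on 28 df.

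**2. Variance under the three analyses.**
- T1 only: 2.3²
- Increase: 2.3² × 2(1 − r)
- T1 adjusted for T0: 2.3² × (1 − r²)

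The ratio of adjusted to T1-only is 1 − r². The ratio of adjusted to increase is (1 − r²) / (2(1 − r)) = (1 + r)/2.

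| r | Adjusted / T1-only | Adjusted / increase | SE T1-only | SE increase | SE adjusted |
|---|---|---|---|---|---|
| 0.3 | 0.91 | 0.65 | 0.336 | 0.397 | 0.320 |
| 0.5 | 0.75 | 0.75 | 0.336 | 0.336 | 0.291 |
| 0.7 | 0.51 | 0.85 | 0.336 | 0.260 | 0.240 |

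The adjusted analysis is at least as precise as either alternative at every r, apart from a degree of freedom or so. The increase is less precise than T1 alone when r is below 0.5. To match the precision of 240 unadjusted T1 scores, the adjusted analysis needs 240 × (1 − r²), about 219, 180 or 123 patients.

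**3. Power at 240.** For a difference of 1.5, adjustment moves power from 99.4% to 99.7%, 99.9% or about 100%. For a t-test on the increase at r = 0.3, the SD is 2.3 × √1.4 = 2.72 and power is 96.5%. If the true difference were only 1.0 (assumed), power would go from 84.5% to 87.7%, 93.0% or 98.6%.

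**4. Baseline imbalance.** With equal SD and ICC at T0, the baseline difference between arms also has SE 0.336. An imbalance of one SE shifts the T1-only estimate by r × 0.336, which is 0.10, 0.17 or 0.24 indicators. It shifts the change-score estimate the other way by (1 − r) × 0.336, which is 0.24, 0.17 or 0.10. Under the same assumptions the adjusted estimate is not shifted.

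**5. Stratum.** The document gives no association between practice organisation and the score, so this gain cannot be computed.

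**The case against.** **No bias and ample power.** Randomisation makes the unadjusted comparison unbiased over repetitions, and the stated inputs already give about 99% power. Both statements stand. The point concerns precision and the credibility of one realised allocation of 30 GPs. It does not show an invalid or underpowered test.

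**The planned SD.** A reader might infer that 2.3 is too small if the test is on the increase, and that the trial is therefore undersized. The SD of the increase does exceed 2.3 when r is below 0.5, but at r = 0.3 power is still about 96%. The inference fails.

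**Exploratory covariates.** A reader might infer that data-driven adjustment threatens the primary test. A t-test has no covariates to choose, and the sentence follows the binary-indicator models. The later open list of fixed effects follows the repeated-measures model. Nor does the article say that covariates are picked by their influence on the treatment effect. In a worst-case simulation without clustering, taking the smallest p-value over all subsets of three or four covariates gave a type I error of about 12–18%. The article describes no such procedure, so that figure does not measure this plan.

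**The Discussion.** A reader might see a contradiction in the naming of chronic conditions. That passage concerns expected results for the indicators, and the factor fits within the open covariate list. It shows that the list is not settled, and no more.

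**The T0 score may be incomplete.** The T0 list does not clearly cover every one of the nine indicators, and newly diagnosed patients may score low on prior care, which could lower r. The first gap applies equally to T1, because the questions are the same. The second reduces the gain (at r = 0.2 the variance is still 96% of T1-only) without turning it into a loss.

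**A condensed article.** Covariate details often sit in an analysis plan. Here, however, the article states a covariate-free primary method, so this is a stated choice that can be improved, not an omitted detail.

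**Conclusion.** The point holds as a matter of efficiency and robustness. The stated primary test leaves unused a pre-intervention measure of the outcome and the randomisation stratum. For r between 0.3 and 0.7, adjusting for T0 lowers the SE by about 5% to 29% against a T1-only test (0.336 to 0.320 or 0.240). Its variance is 65–85% of that of a test on the increase. These figures rest on the assumed correlation, on equal SDs at T0 and T1, and on the planned ICC. The benefit of adding the stratum is unquantified.

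The documents do not support a claim that planned power is inadequate or that the primary type I error is inflated by covariate selection. The failure of the t-test sentence to mention GP clustering, and the mismatch between the stated inputs and 240, are separate points.

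**What to change.** 1. Replace the t-test by one primary model: T1 score on arm, T0 score and practice organisation (single-handed or group), with GP clustering accounted for. State that the effect is the adjusted difference in T1 score. This also settles whether the outcome is a score or an increase.
2. Only for the binary-indicator and other secondary models, list the covariates in advance, including the T0 value of each outcome, and bring the Discussion into line with that list. Where T0 is kept as a response in the longitudinal models, do not also enter it as a covariate.
3. Report any model with covariates found through exploratory analyses as a sensitivity analysis only.

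The cost is wording in the analysis section, made before outcome data are seen. No visit, questionnaire or extra patient is needed. Two checks are required: that each of the nine indicators can be scored from the T0 data in the same way as at T1, and that a simple rule keeps patients with a missing T0 score in the analysis.

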#### GPs

The GP will maintain a record of the participants with an allocated code for each patient. This code is also marked on the questionnaires. The university only receives the patients’ codes and has no access to their names.

A questionnaire is filled out by the GPs with information on the professional characteristics (gender, age, specialty, work time) and of the organizational context, such as single or group practice, regional structures and available resources.

At T0, the GP gives information for each participating patient on demographics, clinical characteristics: comorbidities, BMI, smoking status, PYs smoking, information on respiratory symptoms cough, sputum, dyspnea and severity of dyspnea (Medical Research Council MRC dyspnea scale) spirometry (FEV1/FVC < 0.7) and grade of severity according to GOLD guidelines FEV1 > 80% GOLD I mild COPD, FEV1 50 to 80% GOLD II moderate COPD, FEV1 30 to 50% GOLD III severe COPD, FEV1 < 30% GOLD IV very severe COPD), exacerbation frequency and current (pulmonary) drug therapy.

After 12 months (T1), GPs are asked about smoking cessation counseling activities, yearly influenza vaccination and assessment of physical activity; if ‘yes’ , how was physical activity assessed? Possibilities include anamnesis and objective tests, for example, sit to stand test (STS), six-minute walking test, and ergometer. Also asked about are motivation for physical activity and referral to pulmonary rehabilitation, assessment of exacerbation frequency and health care utilization in previous year, including hospital admissions, emergency department attendances and unscheduled visits. Whether patient education activities are given, verbally and/or via patient booklet, with definition of COPD and information about the main causes, signs and symptoms of COPD is also inquired into, as is whether information on medication and using inhalation devices, face-to-face instruction and demonstration of inhalation technique is supplied. Additionally, whether information on how to identify and manage an aggravation of symptoms (exacerbation) and whether an action plan for exacerbation management, including a written medication adjustment for exacerbation treatment is supplied, is asked about. GPs are also asked whether they educate patients in the practice or refer them to an external COPD program connecting COPD patients with specialized health professionals and community resources (lung associations, support groups).

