### Statistical analysis

#### Calculation of sample size

Based on available data from Switzerland [7,30], and a recently performed cross-sectional survey of our study group, we assume a mean of four regarding the number of performed indicators (primary outcomes 1 to 9 as mentioned above) and a SD of 2.3. We assume an increase in the intervention group in the mean of performed indicators of 1.5. Given a power of 90% and a significance level alpha of 5%, as well as an intracluster correlation coefficient (ICC) of 0.04, we will need eight patients per GP assuming participation of 30 GPs, resulting in 240 patients. Assuming a dropout rate of at least 20% (dropouts are possible on a GP level but also on a patient level, therefore this rate is estimated to be about 20%), we will need 288 patients.

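### For patients who return only one questionnaire, the named t-test and repeated measures ANOVA do not deliver the plan's own intent-to-treat definition

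*Protocol article*

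**What the plan says.** All references are to the protocol article.

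- **Data analysis, intent-to-treat:** the primary analysis follows intent-to-treat where appropriate. This is explained to mean that "all available data from all individuals will be analyzed according to treatment group assignment", whatever treatment was actually received.
- **Data analysis, methods:** a t-test "will be used for independent group comparisons in the primary outcome between control and intervention group". For quality of life, "repeated measures analysis of variance is appropriate". Generalized estimating equations are named for the longitudinal aspect of the separate yes/no indicators.
- **Primary outcome:** the between-arm difference after one year in patient-reported care, described as "total increase in performed measures/fulfilled indicators".
- **Secondary outcomes (scoring details):** the primary outcome runs from 0 to 9, which fits a score at one time point rather than a change.
- **Patient questionnaire:** patients post forms back at two times only, T0 and T1 (12 months).
- **Calculation of sample size:** about 20% loss is expected, and "dropouts are possible on a GP level but also on a patient level".
- **GPs:** at T1, "GPs are asked about smoking cessation counseling activities, yearly influenza vaccination and assessment of physical activity" and further items, per coded patient. The aggregate of these reports is a separate secondary outcome.
- **Patient informed consent:** if a patient discontinues, the material is destroyed unless the patient agrees to its use.

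**The concern.** The article fixes both a principle and the methods, and the two do not match. A patient who returned T0 but not T1 has available data, yet neither the t-test nor a classical repeated measures ANOVA can use them. This is different from a missing-data rule left to the analysis plan, because the methods already chosen determine who is analysed.

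The arms may differ in who returns the T1 form. Only the intervention arm gets the training, the patient education material and the proactive follow-up, and the outcome is the patient's account of that same care. If poorly served patients of trained GPs return T1 less often, and this pattern is absent or weaker among controls, the estimated effect is too large. Other patterns push it the other way. Readers would still take the result as intent-to-treat.

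**Working it through.** **1. Who is left out under each reading**

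| Analysis as named | T0 only | T1 only |
|---|---|---|
| t-test on the increase | dropped | dropped |
| t-test on the T1 score | dropped | used |
| Classical repeated measures ANOVA of CAT, two time points | dropped | dropped |

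T0-only patients are excluded under every reading, so the mismatch does not depend on whether the outcome is a change or a T1 score.

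**2. How many**

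The stated 288 is 240 × 1.2. A 20% loss gives 288 × 0.20 = 57.6, about 58 patients, and leaves 230.4. This is an upper figure for patients with unused data: the 20% is a planning assumption that includes whole-GP dropout, and some of those patients may have no usable data at all. (That 288 × 0.8 falls below 240 is a separate matter.)

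**3. Power**

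Inputs from the sample size section: difference 1.5, SD 2.3, ICC 0.04, 30 GPs, alpha 5% (two-sided assumed). With m patients per GP, the design effect is 1 + (m − 1) × 0.04, and the standard error is SD × √(2 × design effect / n per arm).

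- 240 analysed, m = 8: design effect 1.28; SE = 2.3 × √(2.56/120) = 0.336; 1.5/0.336 = 4.47; power 99.4%.
- 230.4 analysed, m = 7.68: design effect 1.267; SE = 2.3 × √(2.534/115.2) = 0.341; 1.5/0.341 = 4.40; power 99.3%.

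The plan states 90%, so its figure is not reproduced at these inputs; that too is a separate matter. If 2.3 is the SD of the score and the T0–T1 correlation is assumed to be 0, the SD of the change is 2.3 × √2 = 3.25, and power falls from 88.4% to 87.5%. On either reading the lost patients cost about one percentage point or less.

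**4. Bias, in general form**

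In each arm, completer mean − full mean = (proportion lost) × (completer mean − dropout mean). With 20% lost in both arms:

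bias = 0.20 × (gap in intervention arm − gap in control arm).

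Equal gaps give zero. A difference in gaps of 0.5 to 1.5 indicators (assumed) gives 0.10 to 0.30, which is 7% to 20% of the planned 1.5.

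**5. Illustration by simulation**

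Assumed, not in the documents: T0–T1 correlation 0.5, correlation of GP report with patient score 0.6, and odds of return doubling per SD of the driver. The true difference is 1.50.

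| Return depends on | Loss | Completers, T1 score | Completers, increase |
|---|---|---|---|
| GP-recorded care, intervention arm only | 20% / 20% | 1.67 | 1.59 |
| GP-recorded care, both arms | 15% intervention / 30% control | 1.38 | 1.44 |
| Unseen patient T1 score, intervention arm only | 20% / 20% | 1.79 | 1.64 |
| Same mechanism and rate in both arms | equal | 1.50 | 1.50 |

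**6. What a mixed model would do in these settings**

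With equal SDs and correlation 0.5, the model corrects the completer T1 difference by 0.5 × the T0 shift among completers.

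- *Return depends on the T0 score, intervention arm only.* By symmetry with the third row, T0 shifts by 0.29 and T1 by 0.5 × 0.29 = 0.145. Completers give about 1.65 (T1) or 1.50 + 0.145 − 0.29 ≈ 1.36 (increase). The mixed model gives 1.50 + 0.145 − 0.5 × 0.29 = 1.50.
- *First row.* The T0 shift is 0.17 − 0.09 = 0.08. The mixed model gives 1.67 − 0.5 × 0.08 = 1.63, between the two completer figures.

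The model therefore removes bias that runs through data it contains, and does not remove the rest.

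**The case against.** **No completer rule is written down.** This stands. The restriction is inferred from the methods. A reader might infer that the plan openly labels a completer analysis as intent-to-treat, or flatly contradicts itself. The text does not go that far: intent-to-treat applies only where appropriate, its explanation stresses assignment over treatment received, and available data could be read as available cases.

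**The outcome may be the T1 score.** The 0 to 9 range and the planning mean of four support this. It weakens any statement that both questionnaires are always needed. It does not help the T0-only patient, who is dropped either way.

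**Other wording may point to better methods.** Generalized estimating equations can use incomplete records, but they are assigned to the separate binary indicators. The sentence on fixed effects, which follows the ANOVA sentence, may hint at a mixed model for CAT, but it names none and does not reach the primary t-test.

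**Missing data belong in the analysis plan.** True of an imputation rule, and its absence is not the point here. The methods are already fixed.

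**The bias is speculative.** Largely right. A reader might infer from the simulated figures that the effect will be inflated. The documents support no size or direction: the inputs are assumed, and the bias vanishes under the same mechanism and rate in both arms.

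**Imputing from GP reports would solve it.** It returns 1.50 in the first two simulated rows because return was made to depend on the GP record. When return depends on the patient's own T1 score, it still gives 1.66. The GP report is also a separate outcome, supplied by GPs who know their allocation, and it would probably be missing where a whole practice leaves. It does not belong in the primary analysis.

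**Conclusion.** The point holds in limited form. As named, the t-test and a classical repeated measures ANOVA leave observed data unused for patients with one questionnaire, and so fall short of the article's own intent-to-treat definition. Up to about 58 of 288 patients could be affected, if the planned 20% loss occurs and all of those lost left usable data. Power is not the issue. Bias is possible if return depends on care differently by arm; its size and direction cannot be derived from the documents. This rests on the ANOVA being the classical form and on the t-test using observed values only, neither of which the article states outright. It should be corrected, because the remedy is cheap and matches what the plan says it intends.

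**What to change.** In Data analysis:

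1. Analyse the primary score and CAT with a likelihood-based linear mixed model on all available T0 and T1 values: arm, time and arm-by-time as fixed effects, with random effects for GP and patient. Take the arm difference at T1, or in change, as the estimate. The GP effect also brings in the clustering that the sample size assumes.
2. Report the t-test and the ANOVA as sensitivity analyses, labelled as completer analyses.
3. If multiple imputation using the GP-reported T1 indicators is wanted, make it a sensitivity analysis only.

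Elsewhere:

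4. Reconcile Primary outcome with the 0 to 9 range under Secondary outcomes: state whether the outcome is a change or a T1 score.
5. Reconcile the intent-to-treat wording with Patient informed consent: state that data from patients who discontinue are included only where their use is permitted.

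Cost: wording and some extra programming, with no new data. The model relies on a missing-at-random assumption given the T0 and T1 values and covariates it contains. As shown above, it does not remove bias when return depends on care not captured there.
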